### Recruitment

During the recruitment period from November 2019 to December 2020, each site recruited people with diabetes who met the eligibility criteria as part of their routine practice. The sites molded the recruitment procedures based on their local care flow and requirements for the use of PRO in routine diabetes care visits or rehabilitation. At every site, recruitment involves inviting eligible people with diabetes who are registered or scheduled for a diabetes care visit to try the PRO diabetes tool in conjunction with their upcoming visit. Only people with diabetes who provided written informed consent for participation in the study are included. Each site uses different methods of communication with people with diabetes for recruitment depending on their routine care pathways, including using the phone, electronic (app or email), and in-person invitations.

### Data Collection

#### Overview

The data collection and data collection tools are listed in Textbox 3. Data for the primary outcomes are collected using Likert scales and open-ended evaluation questionnaires that are completed by people with diabetes and HCPs in connection with the use of the PRO diabetes tool in routine care and by HCPs at the end of the study. In the mixed methods analysis, qualitative data are collected from transcribed interviews, consultations, evaluations, and debriefing workshops completed during the entire study period.

Data collection tools. The contents of the main data collection tools are available in the multimedia appendices.
**Multicenter patient-reported outcome (PRO) diabetes study**
**core data collection tools**
People with diabetesPRO Diabetes Questionnaire (Multimedia Appendix 6)PRO Evaluation Questionnaires (PRO-EVAL-P; Multimedia Appendix 7)Post-Visit PRO Evaluation Questionnaire (PRO-CON-EVAL-P-SF; Multimedia Appendix 8)Semistructured interview guide for people with diabetes (Multimedia Appendix 9)Baseline sociodemographic data sheet for people with diabetes (Multimedia Appendix 10)Health care professional (HCP)Baseline background data (HCP profile questionnaire; Multimedia Appendix 11)Post-Visit PRO Evaluation Questionnaire (PRO-CON-EVAL-HCP-SF) and evaluation form for algorithm evaluation (Multimedia Appendix 12)Semistructured guide for HCP evaluation workshops (HCP evaluation guide; Multimedia Appendix 13)HCP End-of-Study Evaluation (HCP end-of-study PRO evaluation form; Multimedia Appendix 1)Study siteDiabetes Clinic Resources for Person-Centered Diabetes Care Survey (Multimedia Appendix 14 [57])Site datasheet: Organization, services, population, resources for PRO follow-up

#### Data Collection for Primary Outcome 1: People With Diabetes’ Perceptions of the PRO Diabetes Questionnaire

The perceptions of people with diabetes regarding the PRO Diabetes Questionnaire are evaluated by the people with diabetes at home immediately after completing it using a digital PRO Evaluation Questionnaire (PRO-EVAL-P). This immediate evaluation of the PRO Diabetes Questionnaire by the people with diabetes assesses the perceived relevance of the questionnaire in a realistic scenario before their routinely scheduled visit and allows for both closed and open-ended responses.

#### Data Collection for Primary Outcome 1: People With Diabetes’ Perceptions of the Dialogue and Impact of the PRO Diabetes Questionnaire

This outcome assesses the multi-item and single-item scores from the people with diabetes evaluations using the Post-Visit PRO Tool Evaluation Questionnaire after each visit where the PRO tool was used (PRO diabetes visit). To minimize bias due to social desirability, people with diabetes are informed that their evaluation will be kept confidential, that their HCP will not see their responses, and that their answers will only be used in research after deidentification. These data provide important new information regarding the diversity and variability of individual experiences of people with diabetes when using the PRO diabetes tool in the visit and allow for an analysis of interactions among HCPs, people with diabetes, and setting factors in relation to primary outcomes. Verbatim transcripts of structured interviews conducted with a subset of a minimum of 10 randomly selected people with diabetes in each care setting after their PRO diabetes visit are coded and analyzed for mixed methods analysis.

#### Data Collection for Primary Outcome 2: HCP’s Perceptions of the Use of the PRO Diabetes Tool in Individual Care Visits

These outcome data were obtained from the multi-item and single-item scores for each PRO visit in the study using the HCP evaluations on the Post-Visit PRO Tool Evaluation Questionnaire immediately after or within a few days of the visit. The HCPs will complete informed consent and are informed that the collected data are only used in an anonymized manner. In addition, the HCPs will complete evaluation questionnaires at the end of the study, which evaluate their overall views and attitudes regarding the use of PRO, impact of use of PRO, and requirements for use of PRO.

#### Data Collection for Secondary Outcomes: Predictors, Barriers, Facilitators, and Readiness Factors for the Adoption, Usage, Satisfaction, and Benefits of PRO

Sociodemographic and diabetes profile data were collected for all participating people with diabetes to analyze the known-group and discriminative validity and reliability of the PRO Diabetes Questionnaire together with primary study outcomes by people with diabetes subgroups. A core set of HCP profile data is collected for all HCPs to evaluate primary outcomes by the relevant HCP subgroups. Two comprehensive questionnaires are used—one adapted for use in Denmark for this study from the Primary Care Resources for Chronic Illness Care Questionnaire [57] (Multimedia Appendix 14) and one study-specific questionnaire. The study-specific questionnaire assesses details for each site about the local PRO setup and examines the extent to which the site has resources and services to follow-up on each PRO construct covered by the PRO Diabetes Questionnaire. These data are used to qualitatively analyze relationships between primary outcomes by contextual factors relevant to the delivery of person-centered and psychosocial diabetes care and the RE-AIM analysis.

#### Likert Scale Evaluation Questionnaires of Experience of Use of PRO in Routine Care

We did not identify any previously published PRO evaluation questionnaires that had been specifically designed and validated for our intended large-scale use in routine care settings. The VBHC-PRO-DIA team therefore developed and tested a set of purpose-built Likert Scale evaluation questionnaires in collaboration with people with diabetes and HCPs as part of the PRO tool’s formative evaluation [29]. A first set of long form questionnaires was developed for a hospital-based clinical study to evaluate the impact of the PRO diabetes tool on person-centered communication and autonomy support using multi-item scale scores.

For this study, HCPs from all care settings and a panel of people with diabetes were involved to identify a core set of evaluation questions that were appropriate and acceptable for use in all sites and care settings, which would allow for pooled and comparative analyses. The short-form questionnaires evaluated experiences of people with diabetes and HCPs related to the use of PRO data in their diabetes visit, such as the extent to which the data were used, impact on engagement, dialogue and person-centered care qualities of the visit, impact on self-management and on care quality, and overall satisfaction and interest in continued use. The questionnaires also briefly assess the perceptions of people with diabetes and HCPs on the general quality of the dialogue and aspects of person-centered communication [10,58].

### Data Management

Each research site is responsible for data entry, security, storage, and data quality verification. Of the 10 study sites, 9 opted to use a uniform web-based research data collection system that was purpose-built for M-PRODIA data collection by Aalborg University Hospital. The web-based data collection forms for the M-PRODIA are integrated into the DiaProfil solution for seamless completion by both people with diabetes and HCPs as part of the study procedures. In the hospital study site in the Capital Region, where a separate health platform system is used for PRO data collection and dialogue support, evaluation forms are provided in paper and pencil format, and manual data entry is performed by clinical staff using formats that are comparable with the electronic forms. Double-entry is used for the sample cases. All paper forms and raw data will be stored for 5 years or as required by law.

A comprehensive codebook with operational definitions, numerical codes, and standardized formats for all variables was established for data monitoring, quality control, coding, and harmonization purposes. At multiple points during the study period, sample data are collected to assess data completeness, missing value patterns, and range checks. At the halfway point, the HCP will participate in an interim study review meeting where data quality is evaluated.

### Data Analysis

#### Statistical Methods

Quantitative data (ie, closed-ended questionnaire data and numerical data) will be coded, and all numerical data will be prepared for descriptive analyses and main statistical analyses using IBM SPSS Statistics for Windows (IBM Cooperation). The SAS statistical software package (SAS Institute Inc) is used for multilevel hierarchical regression analyses. Descriptive statistics will be used for continuous (mean and SD) and categorical (frequency and percentage) variables to analyze and compare evaluation data by center and subgroups. The aim of this study is to analyze drop-out data, including nonparticipation, attrition, and completion rates across centers, to characterize the generalizability of findings relating to population reach and outreach to vulnerable populations, and to compare implementation drivers across participating centers. Both parametric and nonparametric statistics were used for group comparisons based on the distribution of each data variable.

Missing value analysis, including the identification of variables missing completely at random or not at random, will be conducted for all variables.

PRO results are scored and analyzed as both raw and scored data using predefined clinical scoring algorithms according to subgroups of adequate sizes for multilevel regression and multilevel logistic regression models [59]. Multi-item scores will be transformed and standardized to a score range of 0-100.

For subgroup comparisons, two-tailed *t* tests and nonparametric statistics, such as the Mann-Whitney *U* test, are used. Multivariate mediation regression analysis will be used to examine the relative contribution of the different participant, treatment, and setting characteristics. Multilevel analyses will be used as feasible and required to separate the variance by people with diabetes, HCP, and care setting. Bonferroni and associated methods will be used to adjust P values for multiple comparisons. Intraclass coefficient analysis will be used to examine the level of agreement between HCPs and people with diabetes on the primary outcomes of the visits, which were evaluated both by people with diabetes and HCPs.

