## Methods

### Study Design

The M-PRODIA is a pragmatic, single-arm, real-world, mixed methods formative feasibility-acceptability pilot implementation study.

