**Figure 2 figure2:**
[figure not shown]
A working model to illustrate hypothesized mechanisms, moderators, and impacts related to the use of the PRO diabetes tool. HCP: health care professional; PRO: patient-reported outcome.

The top part of the model illustrates that completion of PRO at home is hypothesized to impact care through mechanisms of reflection, motivation, and engagement before the visit and through mechanisms of active engagement of the people with diabetes and use of person-centered and value-based care strategies by the HCP during the visit. The use of PRO is hypothesized to lead to different follow-up actions by the health care team, which in turn is hypothesized to lead to different benefits for people with diabetes and HCPs. Both patient, health professional, and care setting factors are hypothesized to potentially moderate the extent to which use of the intervention impacts outcomes for people with diabetes and HCPs. Textbox 2 provides an overview of the main outcomes of this study.

Overview of the main outcomes of the study.

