#### Data Monitoring

Each participating site collects and is responsible for its own data and the delivery of these data to the centralized VBS-PRO-DIA research group at the Department of Endocrinology at Aalborg University Hospital, Aalborg, Denmark, in accordance with specified requirements for the anonymization of data, use of study-specific IDs, and secure data transfers. Furthermore, each site was responsible for ensuring that informed consent was obtained and validated for all participants. All primary analyses were single-arm and noncomparative. Data from each participating site were traceable in the analyses. A data monitoring committee was not deemed necessary because of the accessibility of the data and the nature of the study as a real-world pilot study evaluation.

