### Methodological Considerations

The main strengths of this study are that it combines qualitative and quantitative data to provide detailed insights into the perspective of people with diabetes on the real-world use of PRO and provides a wide range of insights regarding the many factors likely to influence the public health impact potential of the PRO diabetes tool in Denmark.

This pilot study has important limitations. One limitation is the lack of a randomized control group and the other is that the main outcomes are mainly process-orientated and rely solely on self-reported data, which may be subject to bias related to social desirability and recall issues.

The study is not designed to quantify the magnitude of clinical, health, and empowerment-related benefits that may be achieved by using the PRO intervention. The study also does not compare reach and effectiveness performance of different PRO tools, which will be important to determine mechanisms of action. These are important research questions that must be addressed in parallel and planned research. Separate clinical studies by the VBHC-PRO-DIA team are underway to address these issues separately and to examine the impacts of PRO use over time on clinical and health care use indicators and health cost drivers.

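### Mediation regression does not answer the stated question of relative contribution; multilevel regression, reported as association, would

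*Protocol article*

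**What the plan says.** Under Data Analysis, Statistical Methods, the protocol article states: "Multivariate mediation regression analysis will be used to examine the relative contribution of the different participant, treatment, and setting characteristics". It names no exposure, mediator or outcome for this analysis. The same paragraph plans multilevel models, where feasible and needed, to divide variance among patients, health care professionals (HCPs) and care settings.

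The working model under Outcomes (text to Figure 2) gives these factors another role: "Both patient, health professional, and care setting factors are hypothesized to potentially moderate the extent to which use of the intervention impacts outcomes". The mechanisms there are different variables: "completion of PRO at home is hypothesized to impact care through mechanisms of reflection, motivation, and engagement before the visit". For the visit itself, they are active engagement and the professional's person-centered strategies.

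On design, the study is a "pragmatic, single-arm, real-world, mixed methods formative feasibility-acceptability pilot implementation study", and Data Monitoring adds: "All primary analyses were single-arm and noncomparative".

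On measurement, the section on the Likert evaluation questionnaires says that the short forms cover "impact on engagement, dialogue and person-centered care qualities of the visit, impact on self-management and on care quality, and overall satisfaction". Methodological Considerations concedes that the main outcomes "rely solely on self-reported data, which may be subject to bias related to social desirability and recall issues".

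**The concern.** The method does not fit the question. A mediation model asks how much of one variable's association with an outcome runs through an intermediate variable. Asking which participant, treatment or setting characteristics matter most for perceived benefit is a different question, with a standard answer in multivariable or multilevel regression.

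The text also applies mediation to participant and setting factors that the working model presents as potential moderators, and does not mention the variables that the model presents as mechanisms.

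The article says that the results will guide optimization of the tool and the design of later controlled studies. Percentages mediated that answer no stated question, and that may reflect mediator-outcome confounding, could be carried into both as if they described how the tool works.

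**Working it through.** **1. The plan's own figures.** The Sample Size section gives 64 per group (t test) and 63 per group (z test) for 80% power at effect size 0.5, two-sided 0.05. Both reproduce. For the t test, power is 80.1% at 64 and 79.5% at 63. For proportions, 2 × (1.960 + 0.842)² / 0.5² = 62.8, rounded up to 63. They concern two-group comparisons and have no bearing on mediation, for which no figure is given.

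**2. Method against question.** With characteristic X, mediator M and outcome Y, mediation fits

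- M = i₁ + aX + e₁
- Y = i₂ + c′X + bM + e₂

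and reports the indirect effect ab, where total c = c′ + ab. This concerns one X at a time. Relative contribution needs all the characteristics in one model,

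- Y = β₀ + β₁X₁ + … + βₖXₖ + HCP and setting terms + e,

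so that the adjusted coefficients, or the variance explained, can be compared.

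**3. What can be identified.**

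- *Indirect effect of tool use.* X would be use versus non-use. The design has no group without the tool, so X does not vary and a cannot be estimated. The Background says that comparisons of PRO visits with regular visits belong to substudies with separate protocols.
- *Moderation of a tool effect.* This also needs a contrast in tool use, so relabelling the factors as moderators would not rescue the analysis.
- *Indirect effect of a characteristic.* X varies between participants, so a single arm is no obstacle. The estimate still requires that M and Y share no uncontrolled common cause.

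**4. How large the bias could be.** The document gives no values, so everything here is assumed. X is binary with 50% prevalence, the true b and c′ are 0, and shared response style supplies a share ρ of the variance of M and Y. Both paths must be significant at two-sided 0.05; 2,000 replicates per cell. False indirect paths:

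| ρ | X shifts M by 0.3 SD, N=128 | same, N=500 | same, N=598 | X unrelated to M and style, N=598 | X shifts style only, by 0.3 SD, N=598 |
|---|---|---|---|---|---|
| 0 | 3% | 4% | 5% | 0.2% | 0.3% |
| 0.1 | 8% | 57% | 65% | 3.5% | 13% |
| 0.2 | 25% | 91% | 95% | 4.1% | 37% |
| 0.3 | 38% | 91% | 96% | 5.1% | 51% |

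N=598 is the number completing, 500 the recruitment target (125 + 375), and 128 two groups of 64.

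Hand check at N=598, ρ=0.1, shift 0.3:

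- SE(a) = 2/√598 = 0.0818; z = 0.3/0.0818 = 3.67; power Φ(3.67 − 1.96) = 0.956.
- The spurious b is about ρ = 0.1; SE = √(0.99/598) = 0.0407; z = 2.46; power Φ(0.50) = 0.69.
- Product 0.956 × 0.69 = 0.66, against 65% simulated.

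**5. Would plain regression of Y on X do better?** It depends on the source of the error.

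- If X shifts M but is unrelated to style, Y is independent of X by construction. The regression keeps its nominal 5%, while the mediation test reaches 65% to 96%.
- If X is related to style, the regression is misled too. At ρ=0.3 and N=598, the false shift in Y is 0.3 × √0.3 = 0.164; z = 0.164/0.0818 = 2.01; Φ(0.05) = 52%. The mediation test gives 51%.

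**The case against.** The strongest reply is that this is one loosely worded label in a formative study. The analysis is not primary, nothing says that indirect paths will be read causally, and the article disclaims measuring the size of benefit. The working model calls the factors only potential moderators and is to be updated; a characteristic may be a moderator and also act through a mechanism. Exposure, mediator and outcome could be named in a fuller plan. Most of this stands, and it limits the weight of the point. It does not rescue the sentence: a fuller plan can add paths, but the article already pairs a method with a question that the method does not answer.

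A reader might infer three stronger things that the documents do not support.

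- *That a single arm invalidates every indirect effect.* It rules out only those of tool use, which the sentence does not claim to estimate.
- *That mediator and outcome will come from the same post-visit form.* Neither is named. Patients also evaluate the questionnaire at home before the visit, HCPs rate each visit, and the two complete their forms independently. The single-form pairing is a risk, not a stated plan.
- *That response style will make indirect paths significant.* If the characteristic is unrelated to both mediator and style, the rate is about 5% or less. High rates can be produced by assuming that the characteristic correlates with style. Loadings of 0.6 and a correlation of 0.2 imply r = 0.6 × 0.2 = 0.12, and at n=598 about 84% false positives (atanh(0.12) × √595 = 2.94; Φ(2.94 − 1.96) = 0.84). But r = 0.12 also holds between characteristic and outcome, so plain regression errs as often. Such a figure is no argument for replacing mediation.

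**Conclusion.** The point holds as a mismatch of method and question. Mediation regression cannot show the relative contribution of several characteristics, it sits awkwardly with the article's own working model, and in this design it cannot describe how the tool works. This rests on the text alone and needs no simulation.

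The further risk, biased indirect effects of characteristics, is conditional. It needs a common cause of mediator and outcome, and a characteristic related to the mediator or to response style. Under the stated assumptions at N=598, the false-positive rate runs from about 5% or below to 96%. Nothing in the document places this study within that range.

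The primary descriptive analyses are untouched. The matter concerns a non-primary analysis, but is worth correcting because its results are meant to inform the tool and later trials.

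**What to change.** Replace the sentence with: *Multivariable multilevel regression will estimate adjusted associations of participant, treatment, HCP and setting characteristics with perceived outcomes.* Add that these are reported as associations, not as moderation or mechanism of a tool effect, and that such questions are left to controlled studies. The multilevel models that this needs are already planned in the same paragraph.

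If exploratory mediation is kept:

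- name the exposure, mediator and outcome of each path;
- take mediator and outcome from different raters or different times, for example by using the HCP ratings of the same visit;
- add a sensitivity analysis for mediator-outcome confounding;
- label the results hypothesis-generating.

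The cost is one sentence, and some exploratory path estimates are given up or restricted. The change does not remove self-report bias: a characteristic linked to response style will still distort the adjusted associations, so the limitation that the article already states should accompany these results.
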